## Abstract

**Background:**

A growing body of research suggests that the provision of social support can have benefits not only for the recipients but also for the provider. Although initial evidence for affective, self-evaluative and physiological outcomes has been established, the beneficial effects of support provision do not occur consistently across all support interactions, and some interactions may even have detrimental effects on providers. The aim of our experimental paradigm is to enable researchers to test the conditions under which the provision of social support to dyadic partners affects affective, self-evaluative, physiological, and relationship outcomes for the provider. In line with self-determination theory, it is proposed that the provision of support is only beneficial to the provider if it satisfies the three basic psychological needs of autonomy, competence and relatedness. The paradigm allows for the manipulation of the provider's levels of competence (feedback on the effectiveness of their support to the other person) and relatedness (feedback on the alleged level of relatedness perceived by the partner person following the provision of support).

**Methods:**

A priori power analyses resulted in a planned sample size of 250 participants randomized to four conditions: 1) no support provision, 2) support provision without feedback, 3) support provision with feedback on competence, 4) support provision with feedback on relatedness. Primary outcomes are immediate physiological (saliva cortisol, heart rate, heart rate variability, blood pressure), affective (positive and negative affect, anxiety), self-evaluative (e.g., self-esteem) and relationship outcomes. Generalized linear models will be used to compare the four conditions.

**Discussion:**

In a controlled laboratory experiment, this new experimental paradigm manipulates the conditions under which social support is provided. Insights into the conditions under which the provision of social support is detrimental or beneficial to the provider can inform the development of preventive and interventional approaches across a range of life domains, motivational and developmental research across the lifespan (e.g. prevention of care-giver burnout), and applied clinical contexts (e.g. therapeutic interventions).

**Trial registration:**

Pre-registration (2023-11-10): https://doi.org/10.17605/OSF.IO/8SPZW, retrospective registration with more details (2024-10-23): https://www.drks.de/DRKS00034287

**Supplementary Information:**

The online version contains supplementary material available at 10.1186/s40359-024-02319-y.

## Background

A substantial body of research has concentrated on the origins of prosocial behaviour (see e.g. the empathy-altruism debate, [1–7]) or on the consequences of receiving social support from the perspective of recipients. Until recently, the question of whether and how the provision of social support can promote *providers’* health was underexplored [8, 9]. This paucity of research may be attributed to the prevalence of evolutionary, social exchange, and equity theories, which focus on the *costs* for support providers (e.g., loss of own resources, [10, 11]). Research on providers of social support frequently reveals negative consequences for the health of the providers. This is especially the case when the support in question is of an intensive nature, such as caregiving. Indeed, there is a substantial body of evidence indicating that caregiving is associated with poor health outcomes for the caregiver (e.g., [12–15]). Only within the last two decades has evidence emerged suggesting that providers of social support may experience *positive psychological and physiological health benefits* [16–20].

The proposed study 2 of the PROSPECT project (Providing Social Support and Health: Conditions and Temporal Dynamics) sets out to investigate the potential conditions for health-promoting effects of providing support for the provider based on self-determination theory.

### Mechanisms connecting support provision to health outcomes

Social support is usually defined as being directed towards a specific individual e.g., as “an exchange of resources between at least two individuals perceived by the provider or the recipient to be intended to enhance the wellbeing of the recipient” ([21], p. 11). It is hence defined by acts of help as compared to the broader terms of *prosocial behaviour* or *beneficence*, which may include acts of kindness towards strangers and the common good as well (e.g., donating money, smiling at others, engaging in environmental cleanup; [22, 23]).

To explain *how* support provision could result in health benefits, at least three interconnected routes have been described – a *physiological*, an *affective*, and a *self-evaluative* route. Evidence for the physiological pathway comes from studies showing associations between greater support provision and reduced stress reactivity at the cardiovascular and endocrine levels, as well as activation of reward-related neural regions of the brain (e.g., blood pressure, heart rate variability, cortisol response, activity in ventral striatum; [18, 24–28]). Providing support may also have an effect on reported and observed positive affect, happiness, flourishing, generativity, and subjective well-being [29–33]. On the self-evaluative route, providing support to others leads to increases in self-esteem and self-worth [18, 34, 35]. Individuals report pride, self-efficacy and purpose in life immediately after supporting others informally (spontaneous helping acts) but also as a consequence of regular formal (organized) support provision, for example through volunteering [1, 36–38].

In contrast, there is substantial evidence indicating adverse effects on health among those providing support. The primary caregivers of ill family members frequently report an increase in depressive symptoms and a negative impact on their subjective and physical well-being [14, 15]. The combination of distinctive characteristics inherent to the caregiver situation – often marked by exposure to a loved one in distress, a non-voluntary arrangement due to financial strains, and a considerable investment of time and energy – result in exceptional scenarios for the provider. Therefore, it has been proposed that caregiving should be investigated under assumptions different from those of day-to-day support provision [39]. Nevertheless, even daily social support has been observed to occasionally elicit physiological stress responses and heightened depressive symptoms among both formal and informal support providers [40–42].

Meta-analyses often conclude that there is a fine line between experiencing support provision as joyful or burdensome [33, 43–45]. To date, research remains inconclusive and contradictory regarding the point at which the provision of social support positively or negatively affects the physiological, affective, self-evaluative and relationship outcomes of the providers. The question, therefore, is: under which conditions does the provision of social support have a beneficial effect on health and well-being and when does it become a burden?

### Proposed conditions for health benefits of providing support

Several moderators have been investigated independently, to better understand why provided support sometimes fails to show health benefits for the provider. For example, volunteering and mental health are only associated at medium volunteering levels (inversely u-shaped, with extreme investments of time becoming detrimental; [46, 47]). Furthermore, if providers feel overcommitted, not reciprocated, and if support is provided for an extended period of time, negative affective reactions are more likely to occur [4, 48, 49]. However, these discussed moderators of the health effects of support do not explicate the basic cognitive processes that must be initiated for support to be beneficial to the provider. Research on the health effects of social support provision has led to the proposition that providing support is healthy for providers only if it is 1) *voluntary* and 2) *effective* [9]. In the PROSPECT trial, we go one step further by suggesting that providing support to others will only result in benefits for the provider if it serves humans’ basic motivational needs. According to self-determination theory, humans strive to fulfil three basic needs – *autonomy, competence*, and *relatedness* [50, 51]. We propose that the likelihood of beneficial effects for the provider should increase if the support occurs under the conditions that it

is *freely chosen* (autonomy),elicits providers’ *feelings of impact* on the recipients’ problem (competence),or prompts appreciative *feedback* from the recipient (relatedness).

Figure 1 summarizes this proposition.

**Fig. 1 Fig1:**
[figure not shown]
Proposed conditions under which the provision of social support shows benefits for the provider

### Condition of autonomy

There is ample evidence indicating that choosing to help feels better than feeling obliged to do so. For example, Weinstein and Ryan [52] conducted several studies in which participants who were given the choice of how much money they wanted to give, experienced greater emotional and social well-being (increased positive affect, vitality, self-esteem), whereas participants without a choice did not experience benefits. In addition, neural activity in areas linked to reward processing was found to be higher if participants spent money voluntarily instead of mandatorily [53]. Moreover, even caregivers who felt they had a choice in whether they took responsibility for their loved one’s care, reported significantly less stress, physical strain, and detrimental health than those who did not perceive a choice [54, 55]. Thus, fulfilling the basic human need for autonomy appears critical for deriving benefits from providing support [51]. This condition is not manipulated but set for all experimental groups that provide support in our trial.

### Condition of competence

To date, the condition of *perceived effectiveness* has not been operationalized from the provider perspective – neither as a direct measure nor as an experimental manipulation to test its role in making social support provision beneficial. Some studies in the domain of beneficence examined how altering providers’ perceptions of impact affects outcomes. For instance, Aknin et al. [56] found that if the impact of donations to charity was clearly described, participants exhibited heightened positive affect. Furthermore, providers who set a concrete goal of making someone smile through an act of kindness reported higher levels of happiness than those who formed the abstract goal of making someone happy [57]. In other words, observing a concrete impact on the recipient may enhance the provider's *sense of competence* in providing effective support. At present, the evidence on the condition of competence is limited to affective outcomes following acts of kindness (not concrete support) as opposed to objective physiological health indicators.

### Condition of relatedness

We propose that if the support provided elicits positive *acknowledgment* from the recipient, it will satisfy the providers’ need for relatedness. Previous studies have indicated that support from older parents to middle-aged children must *feel rewarding* to decrease depressive symptoms [41]. Although providers benefitted from any compassionate act they provided to their spouses, acts that were *seen* by the recipient led to greater positive affect for the provider [58]. Also, perceiving that one’s partner *appreciates* the provided support was found to moderate the association between giving support and self-reported physical symptoms, in that higher perceptions of appreciation were associated with fewer physical symptoms [59].

Initial studies of combinations of the three proposed conditions for beneficial support show that participants who reported that their support was *effective* and who felt *socially connected* showed activation of the neural substrates of caregiving [26]. A study by Martela and Ryan [60] even found that a gaming condition, in which participants anonymously donated rice to a food program, led to subjective well-being mediated via feelings of autonomy, competence, and relatedness. However, Ko et al. [61] did not find an ‘acts of kindness’-intervention to increase any of the three basic psychological needs. By specifying the needs as mediators, these studies raise the question of whether needs fulfilment is a *consequence* of helping, or whether fulfilling any or all of the three is a pre-condition (moderator) without which support will not benefit the provider. In a seven-day diary study, providers reported better well-being if they perceived autonomy, felt they had improved the recipient’s situation and experienced gratitude for their helping behaviour [62]. Experimental evidence for these three conditions however remains to be accrued.

### Objectives of study 2

The new experimental paradigm was developed to better understand under which preconditions of psychological needs satisfaction (self-determination theory; [51]) social support provision is beneficial for physiological, affective, self-evaluative, and relationship outcomes in providers. We propose that for positive effects to emerge, providers need to support their dyadic partner autonomously (this condition is not manipulated but present in all support conditions), and to build a sense of *competence* and a sense of *relatedness* in providers. Through the experimental manipulation of *competence* and *relatedness*, the causal conditions under which support giving is beneficial for the provider can be extracted from possible confounding variables, such as differences at baseline (e.g., personality, health) and from possible reversed effects (individuals with greater resources providing more support).

The primary objective of this study is to examine whether support providers who receive feedback on the positive impact of their support on the recipient (competence) and on their dyadic partners' appreciation of the support (relatedness) will demonstrate less pronounced increases and/or faster decreases in their physiological stress reactions, more positive affect, more positive self-evaluative and possibly also relationship evaluative reactions than providers who do not receive such feedback. To achieve this, four conditions will be randomized: 1) No support provision (observation condition = control), 2) autonomous support provision without feedback (autonomous support provision only condition), 3) autonomous support provision with feedback on competence (autonomous support provision + competence condition), and 4) autonomous support provision with feedback on relatedness (autonomous support provision + relatedness condition). The following main hypotheses will be tested:

H1: The new paradigm of observing the partner person’s alleged stress and pain responses on a computer screen will influence participants’ physiological, affective, self-evaluative, and relational responses in all conditions (manipulation check).H2: Physiological, affective, self-evaluative, and relationship responses to observing the partner person's alleged stress and pain levels are higher in participants with higher trait empathy.H3: Participants in the support provision conditions will show more beneficial physiological, affective, self-evaluative, and relationship responses than those in the observation conditions that did not get the opportunity to support their partner person.H4: Participants who receive feedback on their support provision – in either the competence or relatedness conditions – will exhibit more beneficial physiological, affective, self-evaluative, and relationship responses compared to participants in the observation and autonomous support provision only condition.H5: Participants in the competence condition will show more beneficial physiological, affective, self-evaluative, and relationship responses than participants in the relatedness condition.H6: Self-reports of competence and relatedness during the experimental manipulation mediate the effects of the condition on physiological, affective, self-evaluative, and relationship responses.

The four conditions and the research model are demonstrated in Fig. 2.

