**Fig. 3 Fig3:**
[figure not shown]
Phases of the study procedure

Part I – Online Survey (baseline). In the first part of this study, participants individually complete the baseline assessment as an online questionnaire on the survey tool SoSci Survey. This questionnaire assesses inclusion and exclusion criteria for the laboratory part, demographics, as well as a series of self-report questionnaires and an empathy test (see measures section).

Part II – Experimental paradigm with manipulation of conditions. The second part of this study will directly manipulate competence and relatedness as potential conditions for effects on immediate physiological, affective, self-evaluative, and relationship outcomes in an experimental paradigm. Participants are invited into the laboratory together with a close dyadic partner. Both dyadic partners are led to believe that their partner person is enduring several runs of stressful tasks in another room of the laboratory. In three conditions, participants will be able to provide social support to their partner persons via text messages in a computer chat window. In two of these conditions, they receive feedback, either that their messages reduced the stress of their partner person (competence condition) or that their partner person feels related to them because of their messages (relatedness condition).

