### Sample size calculation

Meta-analyses summarizing effects of experimental manipulations of prosocial behaviour on well-being resulted in small- to medium-pooled effects sizes from Cohen’s d = .28 [33] to Pearson’s r = .32 (corresponding to a Cohen’s d = .68; 43). Whereas these effect sizes represent support provision vs. no support provision, we are particularly interested in manipulating and comparing the effects of different conditions under which support is provided. Therefore, we base our power analyses on a small n^2^ of 0.02 for the interaction term of time*condition (Cohen, 1992; effect size f = 0.17). We deem a power of 95% desirable to detect effects not only between the ‘support’ to ‘no support’ group, but also between the groups that provide support under different conditions. With 4 between- and 2 within-subject factors entered into a repeated measures ANOVA, G*power estimates a total *N* = 216 (54 per group) to result in a 95% chance to reject the null hypothesis of no significant interaction term [66]. To allow for attrition due to failed manipulation (e.g., participants provide no support despite randomized to chosen support groups), we plan to recruit 250 participants randomized to four groups (125 dyads).

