## Discussion

The current research evidence suggests that individuals who engage in prosocial behaviour tend to report higher levels of subjective well-being [33, 43, 136], greater life satisfaction [137], and a reduced mortality risk [8] among other benefits. Conversely, research has repeatedly demonstrated that, for instance, caregiving can result in burnout and health limitations. The new experimental paradigm described in this protocol, bases on self-determination theory [50], and employs a controlled experimental design to manipulate the conditions of providing social support in a laboratory setting to assess its impact on a range of outcomes, including physiological, affective, self-evaluative, and relationship indicators in dyads.

The objective of the paradigm is to examine the circumstances under which providing social support (via chat messages) to a close social network member (in another room) has beneficial effects for the provider. The observation condition serves as the control condition, in which participants are presented with an alleged stress and pain response by their partner person (on a computer screen), who allegedly endures stress tasks in another room. This observation condition is compared to a condition in which participants are given the opportunity to send supportive chat messages to their allegedly stressed partner person, without receiving any feedback on their supportive efforts (support provision only condition). In order to manipulate perceptions of competence in providers, the third condition (support provision with feedback on competence condition) manipulates partner persons' stress responses shown to providers in a way that after each supportive message a decrease in partner persons’ stress response is shown. The fourth condition manipulates perceived relatedness by showing hugging icons, allegedly sent by the partner person, in response to supportive messages by the provider (support provision with feedback on relatedness condition). The third basic psychological need, autonomy, was not manipulated. However, in each support provision condition, it was highlighted that writing supportive messages is voluntary.

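### H3 and H4 as worded do not separate the effect of giving support from the effect of feedback, and H4's comparator does not match the primary objective

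*Protocol article*

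**What the plan says.** The arms are numbered as in the protocol article: 1 observation, 2 support without feedback, 3 support with competence feedback, 4 support with relatedness feedback.

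- **H3** (Objectives of study 2): "H3: Participants in the support provision conditions will show more beneficial physiological, affective, self-evaluative, and relationship responses than those in the observation conditions".
- **Make-up of the support arms** (Study design, Part II): "In three conditions, participants will be able to provide social support to their partner persons via text messages in a computer chat window", followed by "In two of these conditions, they receive feedback".
- **H4** (same list as H3): the two feedback arms are "compared to participants in the observation and autonomous support provision only condition".
- **Primary objective** (Objectives of study 2): providers with feedback are compared with providers who do not get it. Observers are not providers, so this is arms 3 and 4 against arm 2.
- **Sample size calculation**: 95% power is wanted "not only between the ‘support’ to ‘no support’ group, but also between the groups that provide support under different conditions".
- **Discussion**: the observation arm is said to be compared with the arm that sends messages "without receiving any feedback on their supportive efforts (support provision only condition").
- **Theory** (Abstract, Background): "the provision of support is only beneficial to the provider if it satisfies the three basic psychological needs".

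The remaining hypotheses do not fill the gap. H1 and H2 concern reactions to observing and trait empathy, H5 is arm 3 against arm 4, and H6 is mediation.

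**The concern.** The trial asks under which conditions giving support helps or burdens the provider. That needs two separate quantities: what support does without feedback (arm 2 minus arm 1), and what feedback adds (arms 3 and 4 minus arm 2). H3 and H4 each blend the two. Two thirds of the support side of H3 consists of feedback arms, so feedback alone can make it positive. H4's comparator is half non-providers, so support alone can make it positive. Both hypotheses can therefore be confirmed whichever of the two explanations is true, and a burden from support alone can be averaged away. The document's own theory makes a weak effect in arm 2 a live possibility, so this is not a remote case.

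**Working it through.** **Inputs from the protocol article (Sample size calculation).** 216 participants, 54 per arm, before the allowance for attrition; 250 to be recruited, 62.5 per arm on average; 95% power; a published range of d = 0.28 to 0.68 for support against no support, midpoint (0.28 + 0.68)/2 = 0.48.

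**Assumptions, not stated there.** Two-sided alpha 0.05; pre-post correlation 0.5; equal arms; one outcome; independent participants; no multiplicity adjustment.

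**The plan's own figure.** An eta-squared of 0.02 gives f = sqrt(0.02/0.98) = 0.143. For a group-by-time interaction with 4 groups, 2 measurements and correlation 0.5, lambda = N f² × 2/(1 − 0.5) = 216 × 0.0204 × 4 = 17.6 on 3 and 212 df, and power is 95.2%. So 216 is reproduced. The printed value, "for the interaction term of time*condition (Cohen, 1992; effect size f = 0.17"), would give 156 instead; that is a separate matter. The power figure belongs to the overall interaction, not to any single contrast.

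**Contrasts.** With arm effects 0, d2, d3, d4 relative to observation:

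- H3 pooled = (d2 + d3 + d4)/3
- H4 joined = (d3 + d4)/2 − d2/2

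The variance factor v is 1 for a change score at correlation 0.5 (SD of change = SD), and 1 − 0.5² = 0.75 with baseline adjustment.

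- SE(H3) = sqrt(v × (1 + 1/3)/54) = 0.157 (v = 1) or 0.136 (v = 0.75)
- SE(H4) = sqrt(v × 1/54) = 0.136 or 0.118
- SE(arm 2 − arm 1) = sqrt(v × 2/54) = 0.192 or 0.167

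The ratio of arm 2 − arm 1 to H3 is sqrt(2/(4/3)) = 1.22. Power is from the noncentral t with 212 df, counting only significance in the beneficial direction.

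**Case A: feedback works, support alone does not (0, 0, d, d).** The H3 contrast is 2d/3.

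| d | H3 contrast | contrast/SE (change score; adjusted) | H3 significant |
|---|---|---|---|
| 0.28 | 0.187 | 1.19; 1.37 | 22%; 28% |
| 0.50 | 0.333 | 2.12; 2.45 | 56%; 68% |
| 0.68 | 0.453 | 2.89; 3.33 | 82%; 91% |

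**Case B: support works, feedback adds nothing (0, d, d, d).** The H4 contrast is d/2.

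| d | H4 contrast | contrast/SE (change score; adjusted) | H4 significant |
|---|---|---|---|
| 0.28 | 0.14 | 1.03; 1.19 | 17%; 22% |
| 0.50 | 0.25 | 1.84; 2.12 | 45%; 56% |
| 0.68 | 0.34 | 2.50; 2.89 | 70%; 82% |

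At 62.5 per arm and d = 0.50, the rates are 62% to 75% (case A) and 50% to 62% (case B).

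**Masked harm.** With support alone at −0.3 SD and both feedback arms at +0.5 SD, the pooled estimate is (−0.3 + 0.5 + 0.5)/3 = +0.23 SD. H3 is then significant in favour of support in about 32% (0.233/0.157 = 1.49) to 40% (0.233/0.136 = 1.71).

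**The separating test.** Arm 2 versus arm 1 at zero effect of support is significant in favour of support in 2.5% of trials, whatever feedback does. Its power at 54 per arm is about 30% to 39% at d = 0.28, 70% to 82% at d = 0.48, and 94% to 98% at d = 0.68.

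**The case against.** Several points on the other side stand.

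- **Pooling is not written.** H3 gives no weights. If it meant that each support arm must beat observation, case A would not arise. But the text does not say so, and the Sample size calculation speaks of a single support group against a no-support group. H4 could likewise be read as two separate comparisons, though it names observation and support-only as one comparator. Contrast coding may well be left to an analysis plan that is not shown. The wording of the hypotheses, however, is fixed here.
- **The comparison is foreseen.** A reader might infer that support-only against observation is missing from the study. It is not: the Discussion mentions it, and the Abstract says the four conditions will be compared. What is missing is a main hypothesis tied to it.
- **H3 answers a legitimate question.** Averaged over the support arms, it estimates the effect of having the opportunity to support. A reader might infer that H3 is invalid, or that a positive H3 will be reported as benefit from support alone. The document contains no such decision rule, so neither inference is supported.
- **The theory does not clearly predict zero in arm 2.** Autonomy is present in all support arms, and the section on proposed conditions joins its last two conditions with *or*. The Abstract's wording is stricter. The text is ambiguous, so a null or harmful arm 2 is plausible rather than predicted.
- **The percentages depend on the analysis.** 68% needs baseline adjustment; the repeated-measures contrast used for the sample size gives 56%.

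**Conclusion.** The concern holds in a limited form. As worded, H3 and H4 blend the effect of support with that of feedback, and H4 adds non-providers to a comparator that the primary objective restricts to providers. The blending follows from how the arms are grouped and does not depend on any effect size. Its size does: at 0.5 SD and 54 per arm, H3 is significant in about 56% to 68% of trials with no effect of support alone, and H4 in about 45% to 56% with no added effect of feedback. At 0.28 SD the rates fall to 22% to 28% and 17% to 22%. These figures rest on the pooled reading, two-sided 0.05, a correlation of 0.5, one outcome and no allowance for dyad clustering. The feedback effects are scenarios, because the published range concerns support against no support. The four-arm design already yields the data needed to separate the two effects.

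**What to change.** 1. Keep H3 as an overall contrast, state its weights, and label it 'support with or without feedback'.
2. Add arm 2 versus arm 1, two-sided, as the named test of support alone. This ties the comparison in the Discussion to a hypothesis and allows harm to be shown.
3. Restrict H4's comparator to arm 2: arms 3 and 4 jointly against arm 2, and each against arm 2. This matches the primary objective.
4. Record this as a dated change from the pre-registration, before analysis. The Data Availability section says that data collection was still ongoing.

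**Cost.** No new data are needed, but precision is lost. Arm 2 versus arm 1 has a standard error about 22% larger than pooled H3 (0.192 against 0.157, or 0.167 against 0.136). Its power is only about 30% to 39% at d = 0.28 and 70% to 82% at d = 0.48. The 95% in the Sample size calculation should therefore not be claimed for it. By the normal approximation without baseline adjustment, 95% power would need about 2 × (1.96 + 1.645)²/0.28² = 332 per arm at d = 0.28, and 113 at d = 0.48. Restricting H4 costs a similar amount: the joint contrast against arm 2 has SE sqrt(1.5/54) = 0.167 in place of 0.136, again about 22% more. A non-significant arm 2 versus arm 1 result should be reported with its confidence interval and not read as absence of effect.

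### H4 puts the no-support control in the comparator for feedback, which departs from the primary objective; if that comparator is pooled, an effect of support alone can confirm H4

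*Protocol article*

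**What the plan says.** All of the following stands under 'Objectives of study 2' in the protocol article unless another section is named.

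- **Primary objective.** Support providers who receive feedback are to be compared on their responses with those who do not: "than providers who do not receive such feedback". Only the support-only arm (arm 2) fits that comparator.
- **Arm 1** is "No support provision (observation condition = control"), so its members are not providers.
- **H3** compares the support arms with arm 1: "than those in the observation conditions that did not get the opportunity to support their partner person".
- **H4** concerns "Participants who receive feedback on their support provision – in either the competence or relatedness conditions", and these are to do better "compared to participants in the observation and autonomous support provision only condition".
- **'Sample size calculation'** gives pooled literature effects of d = 0.28 to d = 0.68, says that they describe support versus no support, and says that the study's particular interest is in the different conditions under which support is given. Power is stated only for the overall time-by-condition interaction: 95% with N = 216, 54 per arm.
- **'Planned analyses'** names analyses of variance and linear mixed models between conditions. It gives no rule for deciding H4.

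**The concern.** H4 is the hypothesis that carries the primary objective, namely that feedback on competence or relatedness makes giving support beneficial. Its comparator nevertheless includes people who gave no support. Any general benefit of giving support, which is the subject of H3, can then enter the H4 comparison. On a pooled analysis, a positive H4 could not be read as evidence about feedback.

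The fault could also work the other way. The Background allows that support may burden the provider. Suppose support without feedback leaves providers D below observation and feedback restores them fully. The true feedback effect is then D, but a pooled H4 would show only D/2.

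**Working it through.** **1. The plan's own figure.** Eta squared 0.02 gives f = √(0.02/0.98) = 0.143. With 4 groups, 2 measurements, and an assumed alpha of 0.05 and pre-post correlation of 0.5 (neither is stated), the noncentrality is f² × N × 2/(1 − 0.5) = 0.0204 × 216 × 4 = 17.6 on 3 and 212 degrees of freedom. Power is 95.2%, so N = 216 is reproduced. (The printed f = 0.17 would give N = 156 at the same correlation. That is a separate matter and is not used in steps 2 to 5.)

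**2. Scenario.** Feedback adds nothing and support helps by d. In SD units the means for observation, support-only, competence and relatedness are 0, d, d, d.

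**3. Pooled reading of H4.**
- Contrast: (competence + relatedness)/2 − (observation + support-only)/2 = d − d/2 = d/2.
- Standard error at 54 per arm, 108 versus 108: √(1/108 + 1/108) = 0.136.
- The probability of significance in the favourable direction comes from the noncentral t on 212 df, two-sided alpha 0.05.

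| Support effect d | H4 difference | Noncentrality | H4 confirmed, 54 per arm | H4 confirmed, 62.5 per arm |
|---|---|---|---|---|
| 0.28 | 0.14 | 1.03 | 17.5% | 19.6% |
| 0.50 | 0.25 | 1.84 | 44.8% | 50.3% |
| 0.68 | 0.34 | 2.50 | 70.1% | 76.3% |

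The last column uses the recruitment target, 250/4 = 62.5. A simulation of 20,000 trials at 54 per arm gave 17.6% for d = 0.28 and 70.0% for d = 0.68. The nominal rate is 2.5%.

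**4. Other readings of H4, same scenario, 54 per arm.**
- Success claimed from superiority over observation alone: 39% (d = 0.28) to 98% (d = 0.68).
- Superiority required over observation and over support-only separately: simulated 1.9% and 2.4%, so there is no inflation.

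**5. The comparison named in the primary objective.** Feedback arms versus support-only has expectation d − d = 0 in this scenario. The favourable-direction error is therefore 2.5% whatever the size of the support effect. Its standard error is √(1/108 + 1/54) = 0.167, and its power is:

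| Feedback effect d | 54 per arm | 62.5 per arm |
|---|---|---|
| 0.28 | 39% | 44% |
| 0.34 | 53% | 59% |
| 0.50 | 85% | 90% |

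**The case against.** The strongest objection is that pooling is nowhere stated. H4 can be read as two claims, that feedback beats observation and that feedback beats support-only. On that reading, step 4 shows no inflation. The Discussion also treats observation and support-only as distinct groups: "This observation condition is compared to a condition in which participants are given the opportunity to send supportive chat messages". That sentence is not about H4 and settles nothing either way. The primary objective already names the isolating comparison, and exact contrast coding is commonly left to an analysis plan, which is not shown here.

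Much of this stands. A reader might infer that the plan commits to a pooled test and will report a support effect as a feedback effect. The documents do not say that. The inflation is conditional on pooling, or on accepting superiority over observation as sufficient.

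What the objection does not remove is the mismatch in the text itself. The comparator in H4 differs from the one in the primary objective, H4 names the two arms jointly, and nothing in the article excludes pooling. This is a stated hypothesis, not a coding detail, and an analysis plan that followed its wording could inherit the problem.

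**Conclusion.** H4 as worded does not isolate feedback and does not match the primary objective. If its comparator is pooled, the chance of confirming H4 with no feedback effect is about 17.5% to 70% at 54 per arm over the protocol's own range of support effects, against a nominal 2.5%. If each arm must be beaten separately, the chance stays at or below about 2.5%. These figures assume two-sided alpha 0.05, independent participants (clustering within dyads ignored), equal arms, and d on the scale of the analysed outcome.

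Two stronger statements should not be made:

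- **That about two thirds of trials would falsely confirm H4.** This figure comes from putting the whole planning effect into support versus none. With means 0, d, d, d, the noncentrality of 17.6 equals 54 × 0.75 × d², so d = 0.66. The pooled contrast then has noncentrality 0.33/0.136 = 2.42 and is significant in about 67.5% of trials. That d lies near the top of the 0.28 to 0.68 range, it rests on the assumed correlation of 0.5, and the protocol chose its planning effect with differences among the support conditions in mind.
- **That H4 would merely repeat H3.** Even when pooled, the two contrasts correlate at 1/√3 = 0.58, about one third of shared variance. They overlap but are not the same test.

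**What to change.** Restate H4 as the two feedback arms versus the support-only arm, and leave support versus observation to H3. With H3 as the three support arms versus observation and H5 as competence versus relatedness, the three contrasts are then orthogonal at equal arm sizes. At a minimum, keep the present wording and add that H4 is confirmed only if the feedback arms beat support-only as well as observation.

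The study is pre-registered and the Data Availability statement says that data collection is still under way. Record the change as a dated amendment before analysis.

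The cost is a smaller comparator, 54 instead of 108, and so the modest power shown in step 5: about 39% for d = 0.28 and 85% for d = 0.50 at 54 per arm. No stated power for H4 is lost, because the protocol states power only for the overall interaction. These figures should be known before the analysis.
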